### Outcome measures

#### Primary outcome measure

##### Psychological distress

The primary outcome measure is the total score on the HADS [39-41], which is developed to measure psychological distress in somatic patient populations. It consists of a 7-item anxiety (HADS-A) and 7-item depression (HADS-D) subscale. The HADS shows good psychometric properties in the general medical population, including oncology patients [42]. Internal consistency as measured with Cronbach’s α varied from .84 to .90 [40,42].Test-retest reliability was good as Pearson’s *r* > .80 were obtained [40,43]. Though the cut-off scores of the HADS vary among populations [44], in lung cancer patients they have found to be <8 *versus* ≥8 on the HADS-A or HADS-D [45]. The HADS has been shown to be highly correlated with the Beck Depression Inventory [42]. It has previously been used in intervention studies of mindfulness and shown to be sensitive to change (e.g. [46]).

#### Secondary outcome measures

##### Quality of life (only for patients)

The European Organisation for Research and Treatment of Cancer (EORTC) Core Quality of Life Questionnaire (QLQ-C30) [47] is included, along with the supplemental Lung Cancer questionnaire module (QLQ-LC13) [48]. The QLQ-C30 is designed to use in clinical trials on physical treatments for cancer patients. It incorporates five functional scales (physical, role, cognitive, emotional, social), three symptom scales (fatigue, pain, nausea and vomiting), a global health and quality of life scale and an array of single-item symptom measures. After revisions in the role functioning, global health and physical functioning scale, internal consistency of the subscales varied between .65 and .94, except for the cognitive functioning scale with α varying from .56 to .63 [47,49,50]. Test-retest reliability varied from .63 to .86 [51]. The lung cancer questionnaire module is designed to supplement the core questionnaire and comprises specific symptoms associated with lung cancer (coughing, haemoptysis, dyspnoea, pain) and side-effects from conventional chemo- and radiotherapy (hair loss, neuropathy, sore mouth, dysphagia). While the multi-item dyspnoea scale showed high internal consistency, the pain subscale did not. When combined with the dyspnoea and pain items of the core questionnaire, both the dyspnoea (α = .86) and pain (α = .71) subscale showed high internal consistency. Since the QLQ-C30 and QLQ-LC13 are mainly focused on physical symptoms, we added the items Social Interaction and Alertness Behavior of the Sickness Impact Profile (SIP) [52]. Internal consistency was .94 and test-retest reliability was .92. The SIP correlated with self-assessed sickness and dysfunction [52].

##### Caregiver appraisal (only for partners)

We use the 9-item Self-Perceived Pressure from Informal Care (SPPIC) [53] to assess the extent to which caregiving is experienced as burdensome. To also measure positive aspects of caregiving, the 9-item subscale Care-Derived Self-Esteem of the Caregiver Reaction Assessment (CRA-SE) [54] is included. Internal consistency of the SPPIC was .79 and of the CRA-SE was .73. The SPPIC and CRA-SE were unrelated to each other [55].

##### Relationship quality

To measure relationship satisfaction we included the 10-item Satisfaction subscale of the Investment Model Scale (IMS-S) [56]. The IMS-S starts with 5 items that measure concrete examplars of satisfaction, to enhance the comprehensibility of the global items, which are utilized to form the construct. Internal consistency varied from .79 to .95 and the IMS-S was related to the Dyadic Adjustment Scale. Also, the Mutual Interpersonal Sensitivity scale (MIS) [57] is included to measure communication between partners about the cancer. It contains 18 items and is divided into two scales: open communication and avoiding negative thoughts about the cancer.

##### Spirituality

is measured with the Spiritual Attitude and Involvement List (SAIL) [58] and consists of 26 items, divided into the subscales meaningfulness, trust, acceptance, caring for others, connectedness with nature, transcendent experiences, and spiritual activities. The internal consistency varied from .74 to .88 and test-retest reliability varied from .77 to .92. All subscales, except for connectedness with nature, were related with the Functional Assessment of Chronic Illness Therapy – Spiritual Well-Being Scale.

#### Costs (only for patients)

The cost-effectiveness evaluation is carried out from a societal perspective, considering direct as well as indirect health costs. Data on costs are collected prospectively using a diary in which participants register a) health care utilization: the type of care and its duration, and b) cancer-related absence from work. Unit cost estimates are derived from the national manual for cost prices in the health care sector [59]. Costs of reduced ability to work are estimated using the friction costs method, which results in a more realistic estimate than the human capital approach [60]. Treatment costs of MBSR are calculated using activity-based-costing methods, thus measuring actual resources (time of therapist, time of patients, facilities) used. All unit cost prices are adjusted to 2013 prices. Unit cost estimates are combined with resource utilization data to obtain a net cost per patient over the entire follow-up period.

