**Methods/Design:**

A parallel group, randomized controlled trial is conducted to compare MBSR with TAU. Lung cancer patients who have received or are still under treatment, and their partners are recruited. Assessments will take place at baseline, post intervention and at three-month follow-up. The primary outcome is psychological distress (i.e. anxiety and depressive symptoms). Secondary outcomes are quality of life (only for patients), caregiver appraisal (only for partners), relationship quality and spirituality. In addition, cost-effectiveness ratio (only in patients) and several process variables are assessed.

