### Aims

The aim of the Mindfulness for Lung Oncology Nijmegen (MILON) study is to examine the effectiveness of MBSR compared to TAU in reducing psychological distress in patients with lung cancer and their partners. We hypothesize that patients in the MBSR group will report a lower level of psychological distress (i.e. anxiety and depressive symptoms), higher levels of quality of life, quality of relationship and spirituality than those in the TAU group. Medical and societal costs will be lower in the MBSR versus TAU group. We expect partners in the MBSR group to report a lower level of psychological distress and higher levels of caregiver appraisal, relationship quality and spirituality than their counterparts in the TAU group. With regard to the working mechanisms of the MBSR programme, we will examine changes in mindfulness skills, self-compassion, rumination, intrusion, avoidance and adherence to MBSR.

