#### Baseline

Patients and partners are interviewed to obtain demographics and clinical characteristics, after which they are screened for cognitive impairments with the MMSE [33]. After that, baseline questionnaires, including the Distress Thermometer (DT) [34,35], are administered, followed by randomization. Table 1 shows the assessment instruments and time points at which the questionnaires are administered to patients and partners.

**Table 1 T1:** Measurements and corresponding time points for patient and partner

**Measure**	**Target**	**T0**		**T1**		**T2**	
		**pt**	**pr**	**pt**	**pr**	**pt**	**pr**
MMSE	Cognitive impairments	x	x				
DT	General distress	x	x				
HADS	Psychological distress	x	x	x	x	x	x
QLQ-C30	Quality of life	x		x		x	
QLQ-LC13	Quality of life	x		x		x	
SIP	Impact of sickness	x		x		x	
SPPIC	Caregiver burden		x		x		x
CRA-SE	Caregiver self-esteem		x		x		x
IMS-S	Relationship satisfaction	x	x	x	x	x	x
MIS	Communication about cancer	x	x	x	x	x	x
SAIL	Spirituality	x	x	x	x	x	x
FFMQ	Mindfulness skills	x	x	x	x	x	x
SCS	Self-compassion	x	x	x	x	x	x
RRS-EXT	Rumination	x	x	x	x	x	x
IES	Psychological stress reaction	x	x	x	x	x	x
Diary	Health care use, work absence	Monthly during study period for pt					
Calendar	Mindfulness adherence	Monthly during study period for pt and pr					

*Note.* T0 = Baseline measurement; T1 = Post-intervention measurement; T2= 3-month follow-up measurement; pt = Patient; pr = Partner; MMSE = Mini Mental State Examination; DT = Distress Thermometer; HADS = Hospital Anxiety and Depression Scale; QLQ-C30 = Quality of Life – Cancer; QLQ-LC13 = Quality of Life – Lung Cancer; SIP = Sickness Impact Profile; SPPIC = Self-Perceived Pressure from Informal Care; CRA-SE = Caregiver Reaction Assessment – Care-Derived Self-Esteem; IMS-S = Investment Model Scale-Satisfaction; MIS = Mutuality and Interpersonal Sensitivity; SAIL = Spiritual Attitude and Involvement List; FFMQ = Five Facet Mindfulness Questionnaire; SCS = Self-Compassion Scale; RRS-EXT = Rumination Response Scale – Extended Version; IES = Impact of Event Scale.

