### Statistical analysis plan

#### Sample size

To determine the required sample size, first the sample size was calculated that would be needed for a simple *t*-test and subsequently it was corrected for clustering, repeated measurements and baseline. A two-sided *t*-test on the total HADS score [39,40] (i.e. our primary outcome measure, examining psychological distress (HADS-total), anxiety symptoms (HADS-A) and depressive symptoms (HADS-D)) would require 64 participants in each group to have 80% power to detect a medium-sized difference (effect size = 0.5) with alpha = 0.05. To correct for clustering, we multiplied this sample size of 64 with the design factor (1 + (*n* − 1) * ICC), where *n* denotes the cluster size and where ICC denotes the intra-cluster correlation. In our study, the treatment groups will consist of 14 people, of whom about 7 will be patients. With *n* = 7 and an estimated ICC = 0.01. [72], the correction factor equals 1.06. To correct for repeated measurements and the use of the baseline measurement as a covariate, we multiplied the required sample size by the design factor $\left(\left(1+\rho \right)/2-\rho_{0}^{2}\right),$ where *ρ* denotes the correlation between the post-treatment HADS measurements, and *ρ*_0_ denotes the correlation between the baseline HADS with the post-treatment HADS measurements. With *ρ* = 0.8 and *ρ* = 0.5 as conservative estimates, the second design factor equals 0.65. Consequently, after correction for clustering and covariates, we arrived at a required sample size of 0.65 * 1.06 * 64 = 44 patients per arm. So 88 patients with lung cancer would be required for the study. Based on our pilot study [[name], [name], [name], [name] and [name], in preparation], we expect a 20% drop-out rate. Therefore, we intend to include 110 patients and 110 partners.

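### The economic evaluation is labelled societal and the aims predict lower societal costs, but only patients' costs are collected and partners' programme time is not counted

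*Protocol article*

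**What the plan says.** Under Outcome measures, the article states: "The cost-effectiveness evaluation is carried out from a societal perspective, considering direct as well as indirect health costs". The Aims set the matching hypothesis: "Medical and societal costs will be lower in the MBSR versus TAU group".

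The scope of the cost data is narrower, and three places agree on it:

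- The section heading reads "Costs (only for patients".
- The abstract describes a "cost-effectiveness ratio (only in patients".
- Table 1 assigns the cost diary "Monthly during study period for pt". The next row assigns the practice calendar to both patient and partner.

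The diary covers health care use and "b) cancer-related absence from work". MBSR itself is costed by activity, "thus measuring actual resources (time of therapist, time of patients, facilities) used". The result is a net cost per patient, which enters an ICER per QALY.

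Partners are randomized and treated in this trial. The Sample size section says "the treatment groups will consist of 14 people, of whom about 7 will be patients", and plans for 110 patients and 110 partners. The Background describes partners as giving practical as well as emotional support.

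**The concern.** A societal perspective counts costs whoever bears them. Here half of the planned participants are people whose time, work absence, health care and caregiving are not in the cost data. The plan treats a patient's time in the programme as a real resource and gives the partner in the next seat none.

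Partner programme time is an intervention-arm cost with no counterpart under TAU. Leaving it out lowers the incremental cost of MBSR and makes a finding of dominance easier to reach. The Cost effectiveness section treats dominance as the trigger for a further analysis of savings. A reader of the final report could take a statement of societal savings at face value for a programme delivered largely to couples.

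**Working it through.** **Scope, set side by side.**

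| Item | Patient | Partner |
|---|---|---|
| Health care use (diary) | collected | not collected |
| Work absence (diary) | collected | not collected |
| Programme time (MBSR costing) | listed | not listed |
| Informal care given | not applicable | not collected |
| Therapist time and facilities | listed | no allocation rule stated |
| QLQ-C30 and QLQ-LC13 (source of QALYs) | completed | not completed |

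The label and the hypothesis say societal; the collected items are patient-level.

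**Partners' planned share.** Seats: 7/14 = 50%. Enrolment: 110/(110 + 110) = 50%. The two agree. Both are planning figures, since patients and partners may each join alone.

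**Time omitted per MBSR partner.** The plan states no cost or time total to reproduce, so the inputs are the programme description under Intervention and the homework column of Table 2.

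- Sessions: 8 x 2.5 h = 20 h.
- Home practice per week: 0.75 h x 6 days = 4.5 h.
- Over 7 between-session weeks (Table 2 gives only further sources of information as homework for session 8): 4.5 x 7 = 31.5 h.
- Over 8 weeks: 4.5 x 8 = 36 h.
- Total: 20 + 31.5 = 51.5 h to 20 + 36 = 56 h, before the silent day, whose length is not given.

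The 20 h assume attendance at every session. The 51.5 to 56 h also assume full adherence to home practice.

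**In the whole trial.** If the 110 partners split equally (an assumption), 55 are in MBSR. Sessions alone are then 55 x 20 = 1,100 h, with nothing corresponding in the TAU arm.

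**Conditional money value.** The article gives no hourly rate. At an assumed 5 to 20 euro per hour, sessions alone are 20 x 5 = 100 euro to 20 x 20 = 400 euro per attending partner. No expected total cost or cost difference is given, so whether this would alter the ICER or a dominance result cannot be worked out.

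**Direction.** Partner programme time is positive under MBSR and zero under TAU, so its omission understates the societal incremental cost. Partner health care, work absence and informal care occur in both arms and could rise or fall with MBSR, so their net effect has no known sign.

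**The case against.** The strongest reply is that the restriction is open. It stands in the abstract, in Table 1 and in the heading directly above the sentence on perspective. The cost hypothesis follows the patient hypotheses and precedes those for partners, so it can be read as patient-level, and the QALYs are patient-level too. On that reading the comparison of patients' health care, programme and productivity costs is sound. This stands, and it limits the point to the societal label and claim. It does not rescue the label: measuring effects in patients does not make a patient-only cost societal.

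Three stronger readings are tempting, and the documents do not support them.

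- A reader might infer that partners' seats are left out of therapist and facility costs. The article lists those resources without excluding any part and gives no divisor. Spread over 7 patients, the whole course cost is charged; spread over 14 attendees, half of it falls on patients. Such an allocation rule is commonly left to the full plan.
- A reader might infer that all the partner omissions together favour MBSR. That holds for programme time only.
- A reader might infer that partner time can be costed fully from data already planned. The calendar records the type of practice each day, not its duration, so only session time can be counted directly.

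Two further points also stand. Adding partner costs to an ICER with patient-only QALYs counts the cost of partners' participation without any benefit to them, which tilts against MBSR. And this is a secondary analysis; the primary HADS comparison is untouched.

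**Conclusion.** The point holds in this form: the plan claims a societal perspective and hypothesizes lower societal costs, but its cost data are patient-level and omit partner programme time. That omission understates the societal incremental cost of MBSR by 20 hours of session time per partner who attends every session, and by up to about 51.5 to 56 hours with full home practice, silent day excluded. In euro the size depends entirely on an assumed rate. The sign of the remaining partner costs is unknown, and so is the effect on the ICER. A patient-level comparison of health care, programme and productivity costs remains valid; a conclusion about societal costs would not be supported. The wording should be corrected before the economic results are reported.

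**What to change.** - In the Costs and Cost effectiveness sections, describe the perspective as what is measured: patients' health care costs, MBSR programme costs including patient time, and patients' productivity costs. State that partner costs are excluded.
- In the Aims, limit the cost hypothesis to the same scope.
- Add a sensitivity scenario that values partner session time from attendance records, which the four-session per-protocol rule already requires. Include partner home practice only under a stated assumption of minutes per practice day. State the hourly rate and a range for it.
- Report whether the ICER or a dominance conclusion changes, with the caveat that the QALYs are patient-only, so the scenario counts partner costs without partner benefits.

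The cost is a few sentences and a short additional costing; no new partner diary is needed. The downside is a narrower claim and a less favourable MBSR cost in the scenario.

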#### Process measures

##### Mindfulness skills

are examined with the 39-item Five Facet Mindfulness Questionnaire (FFMQ) [61,62]. The FFMQ is based on an exploratory factor analysis of five mindfulness measures, which allowed items from different instruments to form factors, providing an empirical integration of these independent attempts to operationalize mindfulness. This led to the following five subscales: observing, describing, acting with awareness, non-judging of inner experience and non-reactivity to inner experience. Internal consistency varied from .72 to .93 among the different subscales. Most subscales were related to meditation experience, Psychological Well-Being scales and psychological symptoms, including the Brief Symptom Inventory [61]. FFMQ is sensitive to change in mindfulness-based interventions and is found to mediate the relationship between mindfulness practice and improvements in psychological symptoms (e.g. [63]).

##### Adherence to MBSR

is assessed during the entire study period with a calendar on which participants in the MBSR condition fill out on a daily basis whether they adhere to the mindfulness exercises: either formal practice (e.g. meditation exercise like the bodyscan), informal practice (e.g. activity with awareness) or no exercise. Adherence to MBSR has been shown to mediate the effects of MBCT on depressive symptoms [72].

### Statistical analysis plan

#### Sample size

To determine the required sample size, first the sample size was calculated that would be needed for a simple *t*-test and subsequently it was corrected for clustering, repeated measurements and baseline. A two-sided *t*-test on the total HADS score [39,40] (i.e. our primary outcome measure, examining psychological distress (HADS-total), anxiety symptoms (HADS-A) and depressive symptoms (HADS-D)) would require 64 participants in each group to have 80% power to detect a medium-sized difference (effect size = 0.5) with alpha = 0.05. To correct for clustering, we multiplied this sample size of 64 with the design factor (1 + (*n* − 1) * ICC), where *n* denotes the cluster size and where ICC denotes the intra-cluster correlation. In our study, the treatment groups will consist of 14 people, of whom about 7 will be patients. With *n* = 7 and an estimated ICC = 0.01. [72], the correction factor equals 1.06. To correct for repeated measurements and the use of the baseline measurement as a covariate, we multiplied the required sample size by the design factor $\left(\left(1+\rho \right)/2-\rho_{0}^{2}\right),$ where *ρ* denotes the correlation between the post-treatment HADS measurements, and *ρ*_0_ denotes the correlation between the baseline HADS with the post-treatment HADS measurements. With *ρ* = 0.8 and *ρ* = 0.5 as conservative estimates, the second design factor equals 0.65. Consequently, after correction for clustering and covariates, we arrived at a required sample size of 0.65 * 1.06 * 64 = 44 patients per arm. So 88 patients with lung cancer would be required for the study. Based on our pilot study [[name], [name], [name], [name] and [name], in preparation], we expect a 20% drop-out rate. Therefore, we intend to include 110 patients and 110 partners.

#### Primary analyses

The samples of lung cancer patients and partners will be analyzed separately. Baseline characteristics of the population will be compared between MBSR and control group to ensure that key variables were evenly distributed by randomization. First, analyses will be based on the intention-to-treat approach. Next, we will perform per-protocol analyses with the treatment-adherent sample (i.e. in the MBSR condition participants have to attend at least four of the eight MBSR sessions [73] and in the TAU condition participants do not attend a mindfulness-based programme).

We will use linear mixed models to analyze all outcome variables (i.e. psychological distress, quality of life (only for patient), caregiver appraisal (only for partner), relationship quality and spirituality), with treatment as fixed factor, baseline measurement as covariate and a random intercept based on MBSR group. This procedure will use all observed data in our analyses. In addition, Cohen’s *d* effect size [74] will be reported based on the difference between the group means on baseline and follow-up scores, divided by the pooled standard deviation at baseline and follow-up.

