#### Follow-up assessments

Follow-up assessments take place post intervention and at three-month follow-up. Participants who have access to the internet and have an email address receive the questionnaires online. If not, they receive the questionnaires on paper along with a reply envelope. In case of drop-out, the researcher tries to contact the participant by phone to complete a minimum set of outcome measures and to identify the main reason for drop-out.

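### The listed primary model carries no within-person correlation between T1 and T2, although the sample size depends on it

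*Protocol article*

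**What the plan says.** The Sample size section starts from a two-sided t-test "on the total HADS score [39,40] (i.e. our primary outcome measure") that "would require 64 participants in each group to have 80% power to detect a medium-sized difference (effect size = 0.5) with alpha = 0.05". It makes two corrections. For clustering, with seven patients per treatment group and an ICC of 0.01, "the correction factor equals 1.06". The second is introduced with "To correct for repeated measurements and the use of the baseline measurement as a covariate" and has the form (1+ρ)/2 − ρ₀², where ρ "denotes the correlation between the post-treatment HADS measurements" and ρ₀ is the correlation of baseline with post-treatment HADS. The values 0.8 and 0.5 are taken "as conservative estimates, the second design factor equals 0.65". The result is 44 patients per arm, 88 in total, and 110 after allowing for 20% drop-out.

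On timing, the Follow-up assessments section says "Follow-up assessments take place post intervention and at three-month follow-up", and Table 1 lists the HADS at T1 and T2 for patients and partners. Each person can therefore contribute two post-baseline scores.

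The Primary analyses section gives one model for all outcomes in both samples: "with treatment as fixed factor, baseline measurement as covariate and a random intercept based on MBSR group". It adds that every available observation will be used. It does not say whether T1 and T2 are analysed together, separately or as a mean.

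**The concern.** The sample size takes credit for two correlated measurements per person, but the only random effect in the model sits at another level. An intercept for MBSR group is shared by about seven patients, and TAU participants belong to no MBSR group. It therefore cannot represent the correlation between one person's two scores. If the model is fitted as listed to both visits, the two records of a person are treated as nearly independent and the treatment effect looks more precise than it is. If the visits are split to avoid this, the gain from repeated measurement that produced 44 per arm is lost. Both the error rate and the power of the primary test then depend on a choice that the text does not make.

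**Working it through.** All variances are in units of the HADS variance, and standard errors in HADS standard deviations.

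**1. The plan's own figure.** The t-test at d = 0.5, two-sided α = 0.05 and 80% power needs 63.77, so 64 per group. Clustering: 1 + (7 − 1) × 0.01 = 1.06. Repeated measures and baseline: (1 + 0.8)/2 − 0.5² = 0.90 − 0.25 = 0.65. Then 64 × 1.06 × 0.65 = 44.1, given as 44 per arm; 2 × 44 = 88; 88/0.80 = 110. The arithmetic reproduces.

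**2. What 0.65 assumes.** (1+ρ)/2 is the variance of the mean of two unit-variance scores with correlation ρ. Subtracting ρ₀² removes the part explained by baseline. So 0.65 is the variance of a person's T1/T2 mean given baseline.

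**3. Correlation left after baseline adjustment.** (0.8 − 0.25)/(1 − 0.25) = 0.55/0.75 = 0.733.

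**4. Stacked records, no effective random term (limiting case).** Under independence the variance factor is (1 − 0.25)/2 = 0.375 instead of 0.65.
- Variance understated by 0.65/0.375 = 1.733.
- SE ratio √(0.375/0.65) = 0.76.
- Type I error 2 × [1 − Φ(1.96/√1.733)] = 13.7%.
- With ρ = 0.5 instead of 0.8 this is 9.0%; with ρ = 0.9 it is 15.1%.

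**5. Stacked records, group intercept in the MBSR arm only.** REML simulation with 44 per arm, seven MBSR groups, ICC 0.01, ρ = 0.8, ρ₀ = 0.5, complete data and a Wald z test gave a mean model SE of 0.157 against an empirical SD of 0.176–0.179. Type I error was about 8% to 10.3% across repeated simulations. The group intercept picks up part of the within-person correlation, but not enough.

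**6. Separate models for T1 and T2.** Each person has one record, so the SE does not suffer from this fault, but the factor is 1 − 0.25 = 0.75. Then 64 × 1.06 × 0.75 = 50.9, so 51 per arm, 102 in total, and 102/0.80 = 127.5, so 128 with drop-out. With 44 completers per arm, power is 74.1% (t-test) to 74.9% (normal approximation).

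**7. Listed terms fitted to each person's T1/T2 mean.** Simulation gave a type I error of 4.3%, power of 78% (81% analytically), and a model SE of 0.182 against an empirical 0.177. This reading matches the sample size.

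**8. Stacked records with a participant intercept and a time factor.** Simulation gave a model SE of 0.172 against an empirical 0.178, a type I error of 6.1% (1,500 runs; Monte Carlo standard error √(0.05 × 0.95/1500) = 0.6 percentage points) and power of 80.5% (800 runs) at 44 per arm. This run left out the MBSR-group intercept, so the data's group variance of 0.01 was not modelled.

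| Reading of the model | Type I error | Power at 44 per arm |
|---|---|---|
| Stacked, group intercept in MBSR arm only | about 8–10% | not meaningful |
| Separate visits | 5% at each visit | about 75% |
| T1/T2 mean | 4.3% | 78% (81% analytic) |
| Participant intercept and time | 6.1% | 80.5% |

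**The case against.** The strongest reply is that a journal article condenses. The sentence lists a fixed factor, a covariate and a random intercept; a repeated-measures residual covariance is none of these, so the list does not strictly exclude one. The sample-size text shows that the authors had within-person correlation in mind, and covariance structure is commonly left to the SAP. This reply has weight, and silence alone would be no finding. But the article goes beyond silence: it names a specific random effect, at a level other than the one its sample size relies on.

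Three stronger conclusions are tempting, and the documents do not support them.

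- A reader might infer that no reading gives a 5% test with the stated 80% power. That is wrong: the listed terms fitted to the T1/T2 mean come close (step 7). The article does not state that analysis, and it sits awkwardly with using every observation, because someone seen only at T1 has no such mean.
- A reader might infer that the standard errors are wrong whatever is done. They are wrong for stacked records. Separate-visit models have valid standard errors and lose only power.
- A reader might infer that power collapses to about half. Simulated power of 47–55% does arise if all TAU participants are coded as one cluster, or each as a singleton cluster. The article states neither coding, and an intercept based on MBSR group most naturally means none in TAU.

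It is also fair that the missing time factor does little to the standard error. It matters for defining the estimand and for incomplete data. Part of the excess over 5% in step 5 may come from the z reference with only seven groups.

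**Conclusion.** The point holds in conditional form. The sample-size calculation is sound for a joint T1/T2 analysis, but the model as listed does not carry the correlation on which that calculation depends and does not say how the visits enter. Fitted to stacked records in the most natural way, it gives a type I error of about 8–10%, with 13.7% as the limit. Fitted visit by visit, it is valid but has about 75% power with 44 completers per arm. Only an unstated analysis of person means reconciles the listed terms with the 0.65 factor. The same model serves the primary outcome in patients and in partners, so it should be settled before analysis. These figures rest on the plan's own ρ, ρ₀, ICC and group size, and on reading the second correlation value, 0.5, as ρ₀. The simulations also assume complete data.

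**What to change.** State the primary model as follows: HADS total at T1 and T2, with treatment, time and baseline as fixed terms; a participant random intercept, or an unstructured T1/T2 residual covariance; and the MBSR-group random effect kept, in the MBSR arm only. Name the treatment effect averaged over T1 and T2 as the primary contrast, because that is what the 0.65 factor powers. A treatment-by-time term and visit-specific effects are optional secondary reporting.

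The cost is analysis wording only. No new data are needed, and the sample size of 44 per arm, 88 in total and 110 with drop-out does not change.
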